### 8.4 UNANTICIPATED PROBLEMS

---

#### 8.4.1 DEFINITION OF UNANTICIPATED PROBLEMS (UP)

The Office for Human Research Protections (OHRP) considers unanticipated problems involving risks to participants or others to include, in general, any incident, experience, or outcome that meets **all** of the following criteria:

- Unexpected in terms of nature, severity, or frequency given (a) the research procedures that are described in the protocol-related documents, such as the Institutional Review Board (IRB)-approved research protocol and informed consent document; and (b) the characteristics of the participant population being studied;
- Related or possibly related to participation in the research ("possibly related" means there is a reasonable possibility that the incident, experience, or outcome may have been caused by the procedures involved in the research); and
- Suggests that the research places participants or others at a greater risk of harm (including physical, psychological, economic, or social harm) than was previously known or recognized.

---

#### 8.4.2 UNANTICIPATED PROBLEM REPORTING

The investigator will report unanticipated problems (UPs) to the Institutional Review Board (IRB) and to the DSMB. The UP report will include the following information:

- Protocol identifying information: protocol title and number, PI's name, and the IRB project number;
- A detailed description of the event, incident, experience, or outcome;
- An explanation of the basis for determining that the event, incident, experience, or outcome represents an UP;
- A description of any changes to the protocol or other corrective actions that have been taken or are proposed in response to the UP.

To satisfy the requirement for prompt reporting, UPs will be reported using the following timeline:

UPs will be promptly report to the Children's National IRB and DSMB within 7 business days of the investigator becoming aware of the UP. In the case of a participant death, the IRB and DSMB will be notified within 24 hours.

#### 8.4.3 REPORTING UNANTICIPATED PROBLEMS TO PARTICIPANTS

UPs will be reported to all participants via email and mail if either the IRB determines that this information changes the risk benefit considerations for the trial or if reporting is mandated by the DSMB.

## 9 STATISTICAL CONSIDERATIONS

The statistical analysis plan (SAP) will provide additional details on the planned statistical analysis.

### 9.1 STATISTICAL HYPOTHESES

- Primary Safety Endpoint(s): We will rule out safety concerns. That is, we will rule out the null hypothesis that risk of adverse events post-drug administration will be more than twice the risk during the baseline period (i.e, RR or OR > 2).
- Primary Efficacy Endpoint(s): The null hypothesis is that there is no change from baseline in annualized growth velocity or height SDS over the 12 months of intervention when compared to the 6 month baseline observation period. The alternate hypothesis is that there is a change from baseline in these values.
- Secondary Efficacy Endpoint(s): The null hypothesis is that there is no change from baseline in seated height ratio, arm span minus standing height, or bone age divided by chronological age over the 12 months of intervention when compared to the 6 month baseline observation period. The alternate hypothesis is that there is a change from baseline in these values.

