## 1 PROTOCOL SUMMARY

### 1.1 SYNOPSIS

**Title:** Vosoritide for Selected Genetic Causes of Short Stature

**Study Description:** Short stature can be caused by a number of different genetic defects, many of which directly affect the growth plates. Vosoritide, a C-type natriuretic peptide (CNP) analog, targets chondrocytes within the growth plate leading to increased cell proliferation and hypertrophy. We hypothesize that patients with selected genetic causes of short stature will respond to vosoritide treatment leading to increased growth velocity. This study will enroll patients with selected genetic causes of short stature for whom evidence exists to support the potential for improved growth. The subjects will be followed for a 6 month observation period to obtain baseline growth velocity, safety profiles and quality of life assessments. Subjects will then be treated with vosoritide for 12 months and will be assessed for safety monitoring and improvement in height outcomes. Subjects with a positive response to therapy will be given the option to continue in the extension phase of the study during which they will continue to receive vosoritide until growth cessation.

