#### **Endpoints:**

The primary study endpoints include:

- Incidence of adverse events per subject with particular attention to Grade 3 and 4 adverse events as well as to rates of hypotension
- Change from baseline in age-sex standardized annualized growth velocity after 12 months of treatment
- Change from baseline in age-sex standardized height SDS after 12 months of treatment

The secondary study endpoints include:

- Change from baseline in seated height ratio after 12 months of treatment
- Change from baseline in arm span minus standing height after 12 months of treatment
- Change from baseline in bone age/chronological age after 12 months of treatment

During the extension study, all of the endpoints will remain the same, but the timeframe will be extended from 12 months until growth cessation or subject withdrawal from the study.

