**Study Population:**

The study will include up to 75 pre-pubertal children ages  $\geq 3$  years 0 days AND  $\leq 10$  years 364 days for males,  $\leq 9$  years 364 days for females with selected genetic causes of short stature (as defined below). Children will be recruited throughout the United States and will be brought to Children's National Hospital for all study visits.

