Results of BioMarin's Phase II study were recently published in the *New England Journal of Medicine* . In this Phase II study, they treated 35 patients with achondroplasia in a dose escalation study of vosoritide with doses ranging from 2.5 µg/kg to 30 µg/kg. First, they showed a very reassuring safety profile. Four patients had serious adverse events (grade 3 obstructive sleep apnea, grade 1 tonsillar hypertrophy, grade 3 thyroglossal duct cyst, and grade 3 syrinx – each in 1 patient), all of which were likely associated with the underlying achondroplasia. Only a single patient had a symptomatic hypotensive episode on day 281 of the extension study which self-resolved. The remainder of the safety profile was quite benign with some mild local injection site reactions. Patients receiving the highest two doses of vosoritide had a sustained increase in annualized growth velocity although there was no difference seen between the 15 and 30 µg/kg groups. Over the course of the study, the patients treated with 15 µg/kg achieved a mean gain in height standard deviation score of 1.03 SD. Details of all of the pre-clinical and clinical development data for vosoritide are included in the Investigator's Brochure which accompanies this protocol .

These Phase II results show proof of principle that patients with a severe defect in a chondrocyte signaling pathway (i.e. activating mutation in *FGFR3* causing achondroplasia) can have increases in growth velocity when treated with vosoritide. It is currently unknown how patients with other causes of short stature will respond to vosoritide. Our hypothesis is that patients with selected genetic causes of

short stature, in particular those with evidence suggesting that they affect the same signaling pathways, will also respond to vosoritide treatment with an increase in growth velocity. Furthermore, it is plausible that these patients will have more robust growth responses than those with achondroplasia as achondroplasia is an extremely severe perturbation of chondrocyte physiology.

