### 9.2 SAMPLE SIZE DETERMINATION

This is an exploratory proof of principle Phase I/II study, and therefore, no formal sample size calculations were performed. The study size was chosen based on the feasibility of recruitment in this study time period.

Once the initial sample size of 35 subjects is achieved, we will discontinue recruitment of any genetic cohort with greater than 15 subjects. Additional recruitment efforts will then focus on achieving approximately 10 subjects in each of the cohorts.

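### Section 9.1 says the trial will rule out a doubling of adverse-event risk, which no sample-size check or planned analysis supports and which 75 children could not show for sparse classes such as Grade 3-4 events or hypotension

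*Protocol*

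**What the plan says.** Section 9.1, under the primary safety endpoint(s), reads: "We will rule out safety concerns. That is, we will rule out the null hypothesis that risk of adverse events post-drug administration". The margin it then sets is a relative risk or odds ratio of 2 against the observation period. It names adverse events in general, with no class singled out and none excepted.

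The endpoint in the Synopsis and Section 3 is: "Incidence of adverse events per subject with particular attention to Grade 3 and 4 adverse events as well as to rates of hypotension".

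Section 9.2 says that "no formal sample size calculations were performed" and that the size rests on feasibility of recruitment. Section 4.2 calls the study exploratory and says a later randomized trial will be needed to prove efficacy. Section 9.4.4 describes the end-of-study safety analysis as descriptive: incidence by organ class, preferred term, relatedness and severity. Section 9.4.1 offers a chi-square or exact method for dichotomous endpoints, but nothing aimed at a margin of 2.

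**The concern.** Excluding a relative margin takes events, and events in the control period above all. If none occurs during observation, the ratio has no estimate and a doubling cannot be excluded, even if none occurs on drug. Section 9.1 nevertheless states the exclusion as something the trial will do, in a study whose size was never set against it and whose safety section plans no such comparison.

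At stake is how sparse safety data in children will be read. A handful of serious or hypotensive events could be set beside a stated aim of ruling out safety concerns, although the data could neither confirm nor refute a doubling for those classes.

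**Working it through.** The protocol states no power, event count or alpha for safety, so there is no figure of its own to reproduce. The check asks how often a harmless drug would pass.

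**Inputs from the protocol**
- Size: "The study will include up to 75 pre-pubertal children ages" (Synopsis). All 75 are taken as dosed and followed, which favours the protocol.
- Control period: "The subjects will be followed for a 6 month observation period" (Synopsis), then 12 months on drug.
- Margin: ratio of 2 (Section 9.1).

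**Assumed**
- True rate ratio 1, Poisson counts, events scaled for follow-up time.
- Exact conditional test at one-sided 2.5%, with 5% as a sensitivity check.

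**Test.** Given *m* events in all, the share falling on drug is 12/(12+6) = 2/3 if the drug is harmless. At rate ratio 2 it is 2×12/(2×12+6) = 0.80. A doubling is excluded when the on-drug count is improbably low for a binomial with *m* trials and probability 0.80. With no event on drug, this needs (1/5)^m ≤ 0.025. Since (1/5)² = 0.04 and (1/5)³ = 0.008, at least 3 baseline events are needed. With equal windows the condition is (1/3)^m ≤ 0.025, and 4 are needed.

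**Chance of excluding a doubling with a harmless drug, N = 75**

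| Events per child per 6 months | Expected baseline / on-drug events | One-sided 2.5% | One-sided 5% |
|---|---|---|---|
| 0.0122 | 0.9 / 1.8 | 1.9% | 6% |
| 0.03 | 2.25 / 4.5 | 7.3% | 12% |
| 0.05 | 3.75 / 7.5 | 12.5% | 19% |
| 0.10 | 7.5 / 15 | 25.6% | 36% |
| 0.20 | 15 / 30 | 49.3% | 60% |
| 0.40 | 30 / 60 | 79.8% | 87% |

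**Where the relevant rates may lie.** The only human event counts in the protocol text at hand come from the achondroplasia Phase II study summarised in Section 2.2. Of 35 treated patients, three had a Grade 3 serious event, and for hypotension: "Only a single patient had a symptomatic hypotensive episode on day 281 of the extension study which self-resolved". Follow-up is not given for all 35. Section 2.3.2 mentions 42 months at one dose. Spreading the counts over 42 months, that is seven 6-month periods:
- Grade 3 serious: −ln(1 − 3/35)/7 = 0.0128 per 6 months; × 75 = 0.96 expected baseline events; chance of none = exp(−0.96) ≈ 38%.
- Symptomatic hypotension: −ln(1 − 1/35)/7 = 0.0041; × 75 = 0.31; chance of none ≈ 73%.

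If follow-up averaged only 1 year, the Grade 3 rate would be 3/35 = 0.086 per child-year, or 0.043 per 6 months, and the chance of excluding a doubling would be 11%.

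**What 75 children can support.** The exact two-sided 95% upper limit for 0/75 is 1 − 0.025^(1/75) = 4.8%; for 2/75 it is 9.3%.

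**All adverse events pooled.** At 1 event per child-year, 112.5 events are expected (37.5 + 75) and the time-scaled test excludes a doubling with probability 88%. Two conditions are not met as the protocol stands:
- *Exposure.* Section 9.1 compares risk without stating any time scaling. At 0.1 events per child-year, per-subject risk is 1 − exp(−0.05) = 4.88% over 6 months and 1 − exp(−0.1) = 9.52% over 12. A harmless drug then shows a ratio of 1.95, close to the margin.
- *Capture.* Section 8.2 has adverse events assessed continuously from consent, and Section 8.3.4 has reportable events recorded from consent. Section 8.3.1 limits reporting before the first dose to serious events tied to protocol-imposed interventions. On that narrower rule the baseline count would be far below the true one.

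**The case against.** The strongest reply is that Section 9.1 speaks only of adverse events. A reader might infer that it promises a separate exclusion of doubling for Grade 3-4 events and for hypotension. The documents do not support that: no per-class test is set out, those classes receive particular attention within an endpoint that covers all adverse events, and Section 9.4.4 is descriptive. So it also cannot be said that the trial will report a failed test for each class. This stands. What remains is a sweeping claim that exempts no class, that the analysis section does not carry out, and that would be untenable for the sparse classes.

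It is also fair that the study is openly exploratory and unpowered. That excuses the absence of a calculation but argues against promising to rule something out. A separate analysis plan can choose the test and the time scaling, but it cannot supply baseline events.

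The rates are weak evidence. The Phase II counts are on-drug, in another condition, attributed mostly to that condition, limited to serious events (Grade 3) or symptomatic ones (hypotension), and of uncertain follow-up. Section 2.3.1 (known risks) was not in the text available and may give others. The range in the table therefore carries the argument, and at its upper end the chance reaches 49% to 80%. Frequent blood-pressure readings on Day 1 could raise the hypotension count, but the observation period has no matching schedule, so those extra detections would push the ratio upward.

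**Conclusion.** The point holds as a mismatch between a stated safety conclusion and what the design and analysis can deliver. For all adverse events the shortfall is one of definition (exposure and capture), not necessarily of numbers. For Grade 3-4 events and hypotension, if the claim is taken to reach them, a harmless drug would pass about 2% to 26% of the time at 0.012 to 0.10 events per child per 6 months. Reaching 80% takes about 0.4 per 6 months, roughly nine times the highest Grade 3 rate derived above (0.043). These figures assume 75 children fully followed, time-scaled windows and a one-sided 2.5% test; at 5% the same range is 6% to 36%. The baseline rates are assumptions, not protocol data. The point should be corrected, but it does not invalidate the study.

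**What to change.** 1. Delete the sentence in Section 9.1 promising to rule out safety concerns, and bring 9.1 and 9.4.4 into line so that the stated safety conclusion is one the analysis produces.
2. For Grade 3-4 events and for hypotension, state the conclusion as on-drug incidence with an exact 95% upper limit, quote what the planned size allows (0/75: 4.8%; 2/75: 9.3%), and say that a doubling cannot be excluded for these classes.
3. Keep a ratio-below-2 statement only for all adverse events, as events per unit of exposure (12 versus 6 months), and only once Sections 8.2, 8.3.1 and 8.3.4 are reconciled so that adverse events are captured alike in both periods.

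The first two changes cost wording and one exact limit per class, with no extra children. The third may need adverse-event recording in the observation period to be clarified, and to be widened if it has followed the narrower rule. The safety claim becomes more modest.

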### 9.2 SAMPLE SIZE DETERMINATION

This is an exploratory proof of principle Phase I/II study, and therefore, no formal sample size calculations were performed. The study size was chosen based on the feasibility of recruitment in this study time period.

Once the initial sample size of 35 subjects is achieved, we will discontinue recruitment of any genetic cohort with greater than 15 subjects. Additional recruitment efforts will then focus on achieving approximately 10 subjects in each of the cohorts.

### 9.3 POPULATIONS FOR ANALYSES

The analysis population for all efficacy and safety analysis is all subjects who receive at least one dose of study treatment.

### 9.4 STATISTICAL ANALYSES

#### 9.4.1 GENERAL APPROACH

Analyses on all endpoints will be self-controlled, comparing measurements for each subject during follow-up to the same measurements during the baseline period. Thus, all measurements will be summarized for baseline period (control period), and during follow-up (test drug period). Descriptive statistics will be presented for all measures of change from baseline (mean, standard deviation, median, interquartile range, min and max). Comparisons between baseline period and follow-up period will use a paired t-test for continuous endpoints and a chi-square test for dichotomous endpoints. If there are departures from normality or small samples, we will use Mann-Whitney test for comparison of medians and exact Clopper-Pearson test for comparison of dichotomous endpoints.

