#### 9.4.2 ANALYSIS OF THE PRIMARY EFFICACY ENDPOINT(S)

Growth velocity, based on anthropometric measures, at each scheduled time point will be summarized using descriptive statistics (mean, SD, median, interquartile range, minimum, and maximum). The test of hypothesis of no change from the baseline in growth velocity and height SDS will be conducted via paired t-test. The measurement of height will be converted to age-and sex-appropriate standard score (SDS) by comparison with the CDC reference standards. The Z-score will be summarized similarly to growth velocity. Additional details of the analysis including management of missing data, and approach to handling outliers, non-adherent and lost to follow up subject data will all be included in a separate statistical analysis plan.

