#### 9.4.9 EXPLORATORY ANALYSES

PK parameters will be summarized using descriptive statistics. Changes in bone density Z-score will be analyzed similar to the primary efficacy analyses. Change in cGMP, serum collagen X markers, and changes in QoLISSY will be compared via t-test at each time point compared to baseline. Rates of total anti-vosoritide antibodies and neutralizing antibodies will be reported.

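### Section 9.4.1 declares every comparison within-child, but names independent-groups and single-proportion methods for the fallback and dichotomous tests

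*Protocol*

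**What the plan says.** Section 9.4.1 sets the structure for every endpoint: "Analyses on all endpoints will be self-controlled, comparing measurements for each subject during follow-up to the same measurements during the baseline period". The default tests are "a paired t-test for continuous endpoints and a chi-square test for dichotomous endpoints". The fallback condition is "If there are departures from normality or small samples", with no sample size attached, and in that case "we will use Mann-Whitney test for comparison of medians and exact Clopper-Pearson test for comparison of dichotomous endpoints".

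Section 9.4.2 handles the primary efficacy endpoints separately: "The test of hypothesis of no change from the baseline in growth velocity and height SDS will be conducted via paired t-test". It names no fallback of its own. Section 9.4.3 tests the secondary endpoints in the same way. Both sections leave missing data, outliers, non-adherence and loss to follow-up to the SAP, but not the choice of test.

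On cohort size, section 9.2 says "Additional recruitment efforts will then focus on achieving approximately 10 subjects in each of the cohorts", and section 9.4.7 stratifies the analyses by genetic group. Section 4.2 explains that each child acts as his or her own control so that differences between children are taken out of the comparison.

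**The concern.** The two measurements in each comparison come from the same child, so the test must work on the pair.

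- **Mann-Whitney** ranks all the values together as if they came from two unrelated groups. The spread between children goes back into the error term.
- **The Pearson chi-square test** applied to two periods makes the same independence assumption.
- **Clopper-Pearson** gives exact limits for one proportion and does not compare two periods.

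What is at stake is the own-control design that section 4.2 relies on. It is lost in the small genetic cohorts, where the fallback is most likely to apply. The resulting p-values do not have their nominal error rate. Because the protocol itself fixes these tests, an SAP that follows it inherits the mismatch, and one that corrects it departs from the protocol.

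**Working it through.** The protocol gives no sample size calculation, power, alpha, SD or within-child correlation, so there is no figure to reproduce. From the documents come the cohort size of about 10 (9.2) and the velocity increases of 1.6 and 3 cm/year (5.1, extension phase criteria). Everything else is assumed: two-sided alpha 5%, normal data, and the SDs, correlations and height SDS gain shown. Power comes from simulated pairs, 1,000 to 4,000 data sets per setting, so differences of a point or two mean nothing.

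**Why pairing matters.** Let σ be the between-child SD at each visit and ρ the correlation between a child's two values.
- Variance of the mean change, pairs kept: 2σ²(1 − ρ)/n.
- Variance assumed by an independent-groups test: 2σ²/n.
- Ratio: 1/(1 − ρ).

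**Height SDS, n = 10.** Assume a gain of 0.3 and an SD of change of 0.3. The implied correlation follows from 0.3² = 2σ²(1 − ρ), so ρ = 1 − 0.09/(2σ²).

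| Between-child SD | ρ | Variance ratio | Gain/σ | Mann-Whitney power | Signed-rank power |
|---|---|---|---|---|---|
| 0.4 | 1 − 0.09/0.32 = 0.72 | 3.6 | 0.75 | about 25% | about 78% |
| 0.6 | 1 − 0.09/0.72 = 0.875 | 8 | 0.50 | about 5% | about 78% |
| 1.0 | 1 − 0.09/2.00 = 0.955 | 22 | 0.30 | 0.1% to 0.3% | about 78% |

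The signed-rank test sees a standardised gain of 0.3/0.3 = 1.0 in every row. Mann-Whitney sees only the gain divided by σ.

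**Type I error of Mann-Whitney, n = 10, no effect.** 4.5% at ρ = 0, about 1% at 0.5, about 0.1% at 0.7 and about 0% at 0.9. At ρ = −0.3 it rises to about 7%.

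**Growth velocity, +1.6 cm/year, n = 10 (Mann-Whitney against signed-rank).**

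| SD (cm/year) | ρ = 0 | ρ = 0.3 | ρ = 0.5 | ρ = 0.7 |
|---|---|---|---|---|
| 1.5 | 56% v 53% | 58% v 71% | 60% v 84% | 64% v 96% |
| 2.0 | 36% v 35% | 35% v 48% | 32% v 60% | 31% v 81% |

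At +3 cm/year, Mann-Whitney has 85% to 100% power over these settings, so little can be lost.

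**Dichotomous, 30% against 60%, within-child phi 0.5.**
- n = 10: exact McNemar 5%, chi-square 18% (5% with continuity correction).
- n = 35: exact McNemar 94%, chi-square 78% (66% corrected).

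At n = 10 the paired exact test has little room to reject. It needs at least six discordant pairs, all in one direction: 2 × 0.5⁶ = 0.031, whereas 2 × 0.5⁵ = 0.0625.

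**The case against.** The strongest reply is that the tests that matter most are already right. Section 9.4.2 names the paired t-test for growth velocity and height SDS, and 9.4.3 carries it to the secondary endpoints. That stands. A reader might infer that the primary efficacy result is at risk, but the whole-cohort test as written is paired.

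It is also fair to say that the trigger is inferred. No threshold is given for a small sample, and 9.4.7 does not say that the genetic cohorts will use the fallback. Cohorts of about 10 make it plausible, not certain. Because 9.4.2 has no fallback of its own, the general rule in 9.4.1 is the only one available.

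The error is mostly in the safe direction. With positive correlation Mann-Whitney rejects too rarely, so it does not manufacture efficacy. The study is exploratory, and 4.2 says that definitive proof is not its goal. That lowers the stakes but does not make the test valid.

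Three wider readings are tempting and do not hold:
- That every small-cohort test loses nearly all its power. This needs a correlation of about 0.8 to 0.9 or more, which is plausible for height SDS but not shown. Entry is capped at −2.25 SDS (5.1), which may narrow the spread between children and so lower the correlation.
- That dichotomous tests lose power at n of about 10. The figures above show no such loss.
- That 9.4.9 switches to an unpaired test because it says endpoints "will be compared via t-test at each time point compared to baseline". Section 9.4.1 covers all endpoints and specifies pairing, so this is shorthand.

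**Conclusion.** The mismatch is real and stands in the text of 9.4.1: paired data are assigned an independent-groups rank test, an independent-groups chi-square test and a one-proportion interval. It affects the non-normal or small-sample fallback and the between-period dichotomous comparisons.

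Its size depends on the within-child correlation, which the protocol does not give. For height SDS at n = 10, under the stated assumptions (ρ about 0.72 to 0.96), Mann-Whitney has roughly 0.1% to 25% power against about 78% for signed-rank. For growth velocity at +1.6 cm/year the loss is nil at ρ = 0 and 24 points at SD 1.5 and ρ = 0.5 (84 − 60). It reaches 50 points at SD 2.0 and ρ = 0.7 (81 − 31). At +3 cm/year it is small. For dichotomous endpoints the case rests on validity, not on lost power at n of about 10.

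This is a correction worth making because it is simple and protects the cohort-level analyses. It does not undermine the main analysis.

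**What to change.** In 9.4.1:
- Replace Mann-Whitney with the Wilcoxon signed-rank test on within-child changes, reported with the Hodges-Lehmann estimate and its confidence interval.
- For paired dichotomous endpoints, replace chi-square with McNemar's test and the Clopper-Pearson comparison with exact McNemar. Keep Clopper-Pearson only for intervals on single proportions.
- State when the fallback applies, either as a sample size or by naming the analyses. The exact signed-rank test cannot reach two-sided 5% with fewer than six children (2/2⁵ = 0.0625), so a smaller cohort should be described without a test.

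McNemar does not serve the safety hypothesis in 9.1. It tests equality, not a risk or odds ratio above 2, and it takes no account of 6 months of baseline against 12 months of treatment. If that hypothesis is to be tested, name a within-child method that allows for observation time, such as a Poisson model with child as the cluster and log observation time as offset, and compare its confidence limit with 2. Section 9.4.4 calls the end-of-study safety analysis descriptive, so the two sections should be aligned.

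The test names are a few phrases in the protocol, mirrored in the SAP. The safety method needs a short added paragraph. Neither change adds visits or measurements.
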